## Methods

### Design

This is a randomised controlled trial (RCT), of superiority and unicentric, conducted in parallel with blinding of outcome assessors. The study will have two arms: a multicomponent physical training arm, with progression in volume and intensity, and a control arm, without structured exercise. The study is registered in the Brazilian Registry of Clinical Trials (code RBR-10y6jhrs).

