### Intervention

The intervention will last 24 weeks and will consist of two weekly training sessions in the first 11 weeks, reassessments in the 12th week and three weekly sessions from the 13th to 24th weeks. The planned training will have two major stages, the first consisting of two mesocycles, with progression primarily in volume, and the second consisting of three mesocycles, with progression primarily in the intensity (Table 1).

**Table 1 Tab1:** Structuring of training sessions throughout the Rehabilitation Program (CORE-Study)

**Weeks**	**Structure (Component-type, volume, intensity, progression)**
1	Familiarisation with the training model (focus on learning movements and perceived effort)
2 a 6	**Balance**—3 exercises performed in three sets of 10–30 s, with evolution in time (10 to 30 s) and complexity (stages). Unipedal balance—standing on one foot, balance transitioning from dorsiflexion to plantar flexion, and getting up from a chair and walking in a straight line. The stages are (1) Support from both hands (chair/instructor/wall); (2) One-handed assistance (chair/instructor/wall); (3) No assistance; (4) With eyes closed. **Aerobic (treadmill walking)**—total: 25 min accumulating 15 min of light intensity (RPE: 12/13) and 9–10 min of passive recovery). Duration of blocks in two levels—5 repetitions of 3-min walk with 2-min passive intervals, or 3 repetitions of 5-min walk with 3-min passive intervals. **Resistance (body weight and rubber band)**—Stretch bench press, Sit and Stand, Neutral Rubber Row, Step Up and Down Step and Plantar Flexion (2 sets of 10 to 15 reps at RPE 12/13, interval of 1 min).

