### Control procedure

Patients allocated to the control group will receive recommendations about physical activity and sedentary behaviour. For this, two chapters from the Brazilian Guide to Physical Activity [20] will be provided and explained to patients during a personal meeting. One chapter is entitled “Understanding Physical Activity”, and the other procedural chapter is entitled “Physical Activity for Adults” or “Physical Activity for the Elderly”, depending on the age group of the participants.

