### Randomisation

Patients included in the study will be randomly allocated to one of the two groups. One group will undergo a clinical and functional rehabilitation programme, and the other group will be considered a control, without exercise intervention.

The allocation list will be concealed from all outcome assessors. In order to balance the groups in terms of number of participants, as well as between men and women, a 1:1 block randomisation will be used, stratified by sex. The randomisation process will be carried out using an online software *www.randomizer.org*. This stage will be performed by a researcher who will not be involved in the other experimental procedures of the study.

After baseline evaluations of each patient block, one manager of the study will send the code identifiers of the patients for randomisation by e-mail. This same manager receives by e-mail the allocation list and informs the exercise training providers, while the other manager, responsible for the contact with patients, informs the patients individually about allocation and corresponding procedures (starting training or control procedure meeting).

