### Analysis plan

Continuous sample characterisation variables will have their normality and homogeneity tested by the Shapiro-Wilk and Levene tests, respectively. Those with normal distribution will be described by mean and standard deviation, and the others will be described by median and interquartile range. The categorical variables of sample characterisation will be described by absolute frequency (*n* sample) and relative (%).

To analyse the effects of the rehabilitation programme, generalised estimation equations will be used, adopting the Bonferroni post hoc. Outcomes will be analysed in two ways (by protocol [PP] and intention to treat [ITT]). For this, patients who complete at least 70% of the proposed sessions will be included in the PP analysis. For ITT analysis, all available data of all patients will be used. For this, all patients will be invited for endpoint evaluations, independently of adherence. For missing data, multiple imputation considering the maximum likelihood estimation approach will be used. Effect sizes (ES) will be calculated using Cohen’s *d* test (Cohen 1988), being considered as small values (0.20 ≤ *d* < 0.50), medium (0.50 ≤ *d* < 0.80) and great (*d* ≥ 0.80).

The significance index adopted will be 0.05. The statistical treatment of the data will be carried out using SPSS (Statistical Package for the Social Sciences), version 22.0.

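### The per-protocol rule (at least 70% of sessions) exists only for the training arm, and the plan does not say whether PP or ITT decides the superiority question

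*Protocol article*

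**What the plan says.** The Design section describes the trial so: "This is a randomised controlled trial (RCT), of superiority and unicentric". The comparator is "a control arm, without structured exercise". The Randomisation section repeats this: "the other group will be considered a control, without exercise intervention". Under Control procedure, controls receive two chapters of a national physical activity guide, which "will be provided and explained to patients during a personal meeting".

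The Intervention section schedules, for the training arm, "two weekly training sessions in the first 11 weeks, reassessments in the 12th week and three weekly sessions from the 13th to 24th weeks".

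The Analysis plan states: "Outcomes will be analysed in two ways (by protocol [PP] and intention to treat [ITT"]). The PP set is then defined by one condition, "patients who complete at least 70% of the proposed sessions will be included in the PP analysis". For the other analysis it says: "For ITT analysis, all available data of all patients will be used". It adds that every patient is invited to the endpoint evaluation whatever their adherence, and that missing data are multiply imputed. A single significance level of 0.05 is given. The Primary outcomes section fixes the primary outcome as 6MWD after 24 weeks. No section gives a PP criterion for controls or ranks the two analyses.

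**The concern.** A criterion based on sessions completed has no meaning in an arm without sessions. Taken word for word, it leaves no controls in the PP set and nothing to compare. Taken in the only way that can be run, it filters the training arm on behaviour after randomisation and leaves the control arm whole. The two groups then differ by allocation and also by whatever makes people keep attending for 24 weeks.

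The protocol itself treats attendance as possibly linked to health: under Adherence, repeated absences prompt a call that asks about the patient's clinical situation. A link between attendance and change in walking distance is therefore plausible, although the documents do not establish it.

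This would matter little if PP were labelled supportive. The article instead lists PP and ITT side by side for a superiority trial. As printed, nothing stops a positive PP result beside a neutral ITT result from being presented as evidence of efficacy.

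**Working it through.** **Step 1. What the rule requires in each arm.** The Intervention section gives 11 weeks × 2 + 12 weeks × 3 = 22 + 36 = 58 sessions. The threshold is 0.70 × 58 = 40.6, so at least 41 sessions. In the control arm the same rule is 0 of 0, which is undefined.

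**Step 2. An SD for scale.** The sample size section plans for 50 m, significance level 0.05, 80% power, correlation 0.5 and 22 per group, but states no SD. The figure of 22 therefore cannot be reproduced outright, only solved backwards. For a two-sided two-sample comparison of means, n = 2 × (1.96 + 0.84)² × SD² / 50². With n = 22 this gives SD ≈ 59 m; the t-based version gives 57.8 m (standardised effect 0.865). I use 58 m. With a correlation of 0.5 the SD of change equals the SD of a single measurement, because 2 × (1 − 0.5) = 1. The 58 m can thus be read as an SD of change.

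**Step 3. Expected PP bias when training has no effect.** Assume a share q of the training arm adheres, all controls are kept, and the propensity to adhere correlates r with the outcome. For normal variables, bias = r × SD × φ(z) / q, where z is the normal cut-off that leaves q above it and φ is the normal density. For q = 0.70, |z| = 0.524, φ = 0.348 and φ/q = 0.497, so bias ≈ r × 58 × 0.497 = 28.8 × r metres. That is 5.8, 8.6 and 14.4 m for r = 0.2, 0.3 and 0.5.

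**Step 4. Simulation under no effect.** 20,000 runs, 30 per arm as planned, two-sided t-tests, PP = 21 adherers against 30 controls:

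| r | PP bias (m) | PP type I error | ITT type I error | Either analysis |
|---|---|---|---|---|
| 0 | about 0 | 0.051 | 0.051 | 0.070 |
| 0.2 | 5.7 | 0.066 | 0.049 | 0.086 |
| 0.3 | 8.3 | 0.082 | 0.052 | 0.105 |
| 0.5 | 14.0 | 0.137 | 0.048 | 0.159 |

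The simulated biases agree with step 3; they are slightly lower because the sample is finite. The adherence share also matters. At r = 0.5 the bias is 5.4 m with 90% adhering (PP error 0.065) and 22.4 m with 50% adhering (PP error 0.230).

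**Step 5. What those correlations mean.** Bias equals the non-adherent share times the gap between adherers and non-adherers. At 70% adherence the gap is 5.7 / 0.3 = 19 m for r = 0.2 and 14.0 / 0.3 ≈ 47 m for r = 0.5. The upper value needs a gap almost as large as the 50 m planning effect.

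**Step 6. Two analyses, no selection.** The ITT (30 v 30) and PP (21 v 30) statistics correlate √[(2/30) / (1/21 + 1/30)] = √(0.0667 / 0.0810) = 0.907. The chance that at least one exceeds 1.96 in absolute value is then 0.070 (2,000,000 draws), the same as the r = 0 row above.

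**The case against.** The strongest reply is that the article never says PP will support the superiority claim. It says only that outcomes are analysed in both ways, and an analysis plan that is not shown may name the deciding set. That stands. A reader might infer that the sponsor intends PP to carry the claim, but the text supports only that nothing printed prevents it.

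It is also true that the ITT analysis is sound in this respect: all patients, all available data, endpoint visits offered whatever the adherence, imputation for the rest. Its simulated type I error stays at about 0.05 throughout. The point gives no ground for calling the main comparison invalid.

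A reader might further infer that PP must favour training, or that the bias is a large part of 50 m. The documents do not support either. They give no adherence rate; the 30% in the sample size section is sample loss, not attendance below 70%. They give no adherence-outcome correlation. Patients who feel well may also stop attending. 6MWD is measured repeatedly and analysed by generalised estimating equations, so a deficit already present at baseline and persisting would cancel in a contrast of change; only a difference in change biases the result. The 7% figure applies only if either analysis may declare success.

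Finally, one may say that a session threshold obviously applies only to the arm with sessions. That is the sensible reading, but it is the one that makes the comparison non-randomised. It also leaves in the PP set a control who breaks the Intervention section's ban on concomitant structured exercise. An analysis plan could add a hierarchy, but the stated PP rule would still have no meaning for half of the trial.

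**Conclusion.** The point holds in limited form. The PP set is defined by a criterion that only the training arm can meet, and PP stands beside ITT with no order of precedence in a superiority trial. That controls enter unselected is an inference from silence, but no other reading yields a comparison.

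The size of the bias cannot be known from the documents. It is nil when adherence is unrelated to change in 6MWD. It is about 6 to 14 m for r from 0.2 to 0.5, given 70% adherence, an SD of 58 m back-solved from 22 per group, and selection in the direction that favours training. The sign is likewise an assumption. Type I error for a claim allowed on either analysis is about 7% without selection, and about 9% to 16% over the same range of r. The ITT analysis and the sample size are unaffected.

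**What to change.** State in the Analysis plan that:

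- ITT of 6MWD at week 24 is the sole primary analysis.
- PP is supportive and cannot by itself support the efficacy claim.
- The PP set has a criterion for each arm. For controls this could be compliance with the ban on concomitant structured exercise already in the Intervention section.
- PP results are reported as a non-randomised comparison.

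An adherence analysis by two-stage least squares, with allocation as the instrument, is optional and at most supportive. It assumes that allocation acts only through sessions attended. That is doubtful here, because the training arm also has messaging groups and calls after absences (Adherence section), and weekly adverse-event questionnaires against six-weekly contact for controls (Adverse events section).

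The cost is a few sentences, plus a consistent record of controls' concomitant exercise. Sample size and outcome assessments do not change. The downside for the sponsor is that a result positive only in PP could no longer be claimed as efficacy.

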### Dissemination policy

The findings of this trial should be disseminated in the following forms:Individual reports to participants;Manuscript published in peer-reviewed periodicals;Summaries with language appropriate for the general population on social media;Presentations at scientific conferences;Work meetings with health professionals.

The flowchart of the study is presented below (Fig. 3).

**Fig. 3 Fig3:**
[figure not shown]
Study flowchart—in article, title of figure below

## Discussion

Despite the millions of deaths that have occurred due to the COVID pandemic in the world, fortunately, the number of patients who have recovered from COVID-19 is increasing. However, a large portion of these patients present with a collection of complications after the acute phase of the disease, which are not necessarily related only to patients who had a severe condition and were hospitalised [52]. There are currently reports that address epidemiological aspects of the so-called syndrome post-COVID-19 or long COVID. As an example of this new context, a cohort study composed of 222 patients who were hospitalised with SARS-CoV-2 infection sought to describe the prevalence of symptoms related to post-COVID-19 syndrome and concluded that 56.3% of patients reported new persistent symptoms or symptoms more than 21 days after diagnosis, and 25% of these patients were unable to return to baseline health status after recovery from the acute infection [53]. On the other hand, an Italian study evaluated 143 patients after hospital discharge after recovery from the acute phase of COVID-19, and they found that 87.4% of these patients reported persistence of at least one symptom 60 days after the onset of the first symptom [54].

Complications related to post-COVID-19 syndrome vary from organ dysfunctions, such as of the heart, lungs and brain [55], to fatigue, headaches, attention disorder, hair loss and dyspnea, which are five among the 55 manifestations considered most prevalent, according to a recent systematic review with meta-analysis [55]. Another important factor related to post-COVID-19 syndrome is the likely psychosocial impact. Reports of persistent malaise and exhaustion similar to chronic fatigue syndrome, in addition to predisposing patients to greater physical weakness, favour the emergence or worsening of emotional disorders and may also leave them susceptible to depression, anxiety, stress disorder, post-traumatic stress disorder and substance use disorder. Additionally, among the complications presented and related to post-COVID-19 syndrome, fatigue is one of the most prevalent, and it greatly contributes to an increase in sedentary behaviour, as the individual is less willing to carry out work activities [56]. This issue should be highlighted as sedentary behaviour contributes to a higher incidence and mortality from cardiovascular disease, cancer, type 2 diabetes, and all-cause mortality [56].

Based on the aforementioned context, it is highly relevant to conduct rehabilitation programmes that provide and enhance the recovery of these individuals, taking into account the complexity existing in the context of COVID-19. We emphasise that our study takes this complexity into account, both in the structuring of the intervention, of a multicomponent nature, as well as in the choice of outcomes, which cover manifestations of the most diverse organic systems, namely behavioural, clinical, morphological, psychosocial and, above all, functional.

As for the prescription of physical training, there is consistent evidence with a rehabilitative approach [56–61] that highlights its supporting therapeutic role in the treatment of numerous diseases and communicable and non-communicable chronic diseases [60], where there is an inverse relationship between regular practice of physical activity and physical exercise and premature mortality [62]. But when talking about rehabilitation programmes in individuals affected by symptoms arising from COVID-19, there is not, to date, sufficient evidence that can guarantee safe recommendations regarding the prescription of physical training, despite the constant emergence of new intervention studies within this perspective. We also emphasise that the literature that addresses both the prescription of exercise training within a biopsychosocial perspective and the aspects inherent to the variables of monitoring and patient safety is limited. Since COVID-19 is a multisystem disease, there is a need for studies that consider the complexity of post-COVID-19 rehabilitation and which are methodologically robust, as in the case of randomised and controlled clinical trials. Of the studies that we have observed so far, all of them present interesting rehabilitation proposals, but at the same time they have important limitations. These limitations range from intervention characteristics (1—short or medium-term intervention periods, 2—only one component/trained physical quality) [19, 63–66] to methodological limitations (1—patient allocation non-randomised, 2—lack of a control group, 3—absence of blinding of the evaluators, 4—absence of details regarding the monitoring of parameters that contribute to patient safety) [ 63, 64, 67].

Concerning the investigation of the effects of physical training on individuals with sequelae from and related to COVID-19, it is relevant to analyse the effect of this training within a multicomponent perspective, especially due to the heterogeneity of these sequelae, which compromise different systems of the human body to different magnitudes. There are a multitude of methods and possibilities for prescribing multicomponent physical training, but in the context of the rehabilitation of post-COVID-19 patients, this training must be especially structured based on the aerobic and resistance components since the physical qualities related to these components are greatly impaired in patients who have experienced COVID-19 in a moderate or severe form. Therefore, conducting an RCT with a multicomponent training intervention, with gradual progression of dosage (volume and intensity) can provide important information about the effectiveness of the present rehabilitation programme.

The design of the present study stands out for the fact that it seeks to test whether the combination of physical training performed from aerobic, balance and resistance exercises, with gradual and individual progression of training loads. Thus, it is expected that the proposed intervention will provide positive results in terms of neuromuscular, respiratory, cardiorespiratory, cardiovascular, behavioural and psychosocial parameters in functional capacity and autonomy and in the quality of life of those people who have not fully recovered from COVI-19 after the phase acute illness. It should also be noted that of the RCTs that aim to evaluate the effect of physical exercise for this population, there is no knowledge to date of the existence of any study that has been conducted for periods longer than 12 weeks. Therefore, it is understood that our study is pioneering in this aspect as it proposes the follow-up of individuals with persistent symptoms of COVID-19 for a period of 24 weeks, who, later, should be tracked in an observational follow-up for at least 5 years.

Based on the aforementioned context, we highlight how relevant it is to measure the long-term impact that physical training can provide to patients in each of the variables that will be analysed. As for the outcomes of our study, we expect that the physical training prescription performed, based on all the previously highlighted criteria, can present promising results even after 24 weeks of physical training supervision, especially regarding our primary outcome (functional capacity according to the 6-min walk test).

We understand that the results of the present study may allow for benefits to be extrapolated which are directly related to the target population of the study; this may have important implications for the optimisation of physical training prescriptions in outpatient rehabilitation programmes.

This clinical trial protocol and its future findings should have important implications. Exercise professionals will be able to use the practical approach adopted for better conduct of its training prescriptions for this population, especially by customisability of protocol. From a theoretical perspective, there is pioneering analysis of the medium (11 weeks) and long-term (24 weeks) effects of the progressive multicomponent training with respect to several important outcomes, using robust methodological control. Clinically, the study will allow a new and safe tool for clinical decision-making, providing data about safety, adherence and the efficacy of multicomponent training in post-COVID-19 scenarios. Finally, the present training protocol, being evidenced as safe and effective, will support the creation of exercise programmes for post-COVID rehabilitation in public health, as well as the performance of other studies with a more pragmatic approach.

### Trial status

Protocol version 1.0, 1 December 2022. The inclusion of patients in the trial will occur in blocks of 6 to 8 patients. The first block was recruited in November 2021 and the last block was recruited in October 2022. All patients included are evaluated for 2 weeks, followed for 24 weeks (intervention period), reavaluated for 2 weeks and included in an observational step, probably with 5 years of duration.

## Data Availability

All materials described in the manuscript, including all relevant raw data, will be freely available to any scientist who wishes to use them for noncommercial purposes, without violating participant confidentiality.
